### Primary Outcome: Gait Speed

The assessments will be performed at ADEMBI by blinded research staff at baseline (T1), 3 months (T2), and 6 months (T3). Participants will walk through a 10-meters corridor at their own habitual speed. The time spent in performing the test will be measured through photoelectric cells (Polifemo, Microgate, Italy), and afterwards, gait speed calculated Participants will be allowed to wear their own footwear, orthoses, and prescribed usual assistive device (crutches, canes). This test will be performed as the first assessment to avoid possible muscle fatigue.

### Secondary Outcomes

Secondary outcomes will include physical and cognitive performance tests (Table 2), and clinical, fatigue and quality of life assessments (Table 3), and the measurement of circulating inflammatory cytokines.

**Table 2 T2:** Physical and cognitive assessment tests and questionnaires.

**Test (references)**	**Functions/Parameters**	**Description**
Handgrip strength test (Jamar dynamometer) (46)	Dominant hand grip strength	Squeeze the dynamometer with maximum isometric effort for about 5 s
Timed Up and Go test (47)	Dynamic balance	Get up from a chair without upper-limb assistance, walk 3 m at a normal pace, turn and sit back in the chair
Short Physical Performance Battery (SPPB) (48)	Lower extremity function: static balance, gait speed, and getting in and out of a chair	Side-by-side, semi-tandem, and tandem stands (10 s); 4 m walk test at comfortable speed; and 5 quick sit to stands from a chair without upper-limb assistance
Berg balance test (49)	Postural stability	Performance of 14 functional tasks
Yale Physical Activity Scale (50)	Physical activity	Type, amount, pattern, and perceived difficulties of performed physical activities throughout daily living
Montreal Cognitive Assessment (MoCA) (51)	Cognitive dysfunction	Covered domains: attention and concentration, executive functions, memory, language, visuoconstructional skills, conceptual thinking, calculations, orientation

**Table 3 T3:** Muscle spasticity, fatigue, and health related quality of life assessment tests and questionnaires.

**Test (References)**	**Functions/Parameters**	**Description**
Modified Ashworth Scale (MAS) (52)	Spasticity	Graduation of the resistance encountered during passively stretching flexor and extensor muscle groups of bilateral hip, knee, and ankle
Modified Fatigue Impact Scale (MFIS) (53)	Physical and mental fatigue	21-item scale measuring perceived fatigue over the last four weeks
EuroQol-5 (54)	Health related quality of life	Covered domains: mobility, self-care, usual activities, pain/discomfort, and anxiety/depression

Participants will self-report their age, gender, marital status, employment situation, and Barthel index (49). Physical and cognitive examination will include the following (Table 2): the handgrip strength test (50) (Jamar dynamometer), Timed Up and Go test (51), Short Physical Performance Battery test (52) (SPPB), Berg balance test (53), Yale Physical Activity Survey (54) (YPAS), and Montreal Cognitive Assessment (55) (MoCA). Clinical information will be determined by the Modified Ashworth Scale (56) (MAS) and the number of outbreaks and falls during the studied period. Fatigue will be assessed by the Modified Fatigue Impact Scale (MFIS) (57) and health related quality of life by the EuroQol-5 [(18); Table 3].

Plasma levels of pro-inflammatory (Interferon γ, Interleukin-12, Tumor necrosis factor-α, Interleukin-17, and Interleukin-6) and anti-inflammatory (Interleukin-6, Interleukin-4, Interleukin-13, Interleukin-10 and Tumor growth factor-β) cytokines will be assessed using Simoa HD-1 technology. Assays will be performed according to the manufacturers' instructions. Briefly, a two-step assay procedure will be utilized. Standards will be prepared with calibrator diluent according to lot-specific concentrations provided by the manufacturer. Samples will be prepared as directed using a sample diluent off-line.

### Safety Assessments

All co-existing diseases or conditions related to the intervention will be treated according to prevailing medical practice. They will be reported as adverse events. In cases where the functionality of a participant decreases due to an adverse consequence (e.g., skin injuries, falls, etc.) the program will be individualized and adapted for that person upon her/his return.

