### Inclusion and Exclusion Criteria, Recruitment, and Randomization

Subjects will be considered eligible for the study if they fulfill all of the following criteria: (a) aged ≥ 18 years, (b) diagnosis of MS according to McDonald criteria (45), (c) moderate to severe gait impairments defined by an Expanded Disability Status Scale (EDSS) score ranging from 4.5 to 7 (46), and (d) the need for one or two canes or crutches for walking outdoors.

Participants will be excluded if they (a) have a neurological pathology in addition to MS, (b) have some musculoskeletal disorder that could limit the extension of the hip and knee or the plantar flexion of the ankle, (c) have suffered an outbreak of MS during the 3 months prior to the start of the study, (d) are under non-stable pharmacological treatment or with treatments expected to be modified during the study, or (e) have received treatment with botulinum toxin in the 12 weeks prior to the beginning of the study.

Recruitment will be done at ADEMBI. Informative meetings will be organized to provide detailed oral and written information about the study, including objectives, studied variables, and methodology, to both potential participants and their families. Participants will sign, indicating informed consent, after fully understanding the study. Using a coin-tossing sequence generation, participants will be randomly allocated at a 1:1 ratio to either the control group (CG) or the intervention group (OR). The assignment will be conveyed via sealed opaque envelopes.

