### Control Group Intervention (CG)

Subjects in the CG will participate in the routine physiotherapy sessions provided to all patients with MS at ADEMBI. ADEMBI is a reference MS center for providing expertise and specialized rehabilitation to people with MS, where all the participants receive individualized assistance throughout the year following the latest recommendations and clinical guidelines for managing the disease. The duration of each session is one hour; in these sessions, conventional methods of physiotherapy are provided to control spasticity, maintain articular range and exercise balance.

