### Statistical Considerations

Data analysis will be performed using the IBM SPSS Statistics 24 statistical software package (SPSS, Inc., Chicago, IL). First, all data will be checked for normality of distribution using the Shapiro-Wilk test. Results will be expressed as means (with standard deviations) for continuous and normally distributed variables and as medians (with interquartile ranges) when normality of data cannot be assumed. Categorical variables will be described in frequency counts and percentages. Tests for baseline comparisons will be selected based on the nature and distribution of the data: Student's-t test for continuous and normally distributed variables, Mann-Whitney test for non-normally distributed continuous variables, and Chi-squared test for categorical variables. To test the effects of training interventions, mixed-designed ANCOVA-s or the Friedman test, including baseline measurements as covariates, will be performed for all studied variables. In cases where a significant F-value is found, LSD *post hoc* procedures will be performed for pair-wise comparisons. The level of statistical significance will be set at *p* < 0.05 for all computations.

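### The adverse-event rule is ambiguous and ties reporting to relatedness, so events other than falls and outbreaks may be captured unequally between the arms

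*Protocol article*

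**What the plan says.** The section Safety Assessments contains the whole rule. It says what will be treated and then that the same items are what is reported: "All co-existing diseases or conditions related to the intervention will be treated according to prevailing medical practice. They will be reported as adverse events". The next sentence concerns loss of function: "In cases where the functionality of a participant decreases due to an adverse consequence (e.g., skin injuries, falls, etc", and says that the program will then be adapted for that person. No arm is named or excluded.

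Two other places bear on the point. Secondary Outcomes collects "the number of outbreaks and falls during the studied period", with no condition on cause and no restriction to one arm. Statistical Considerations states that the effect tests, "including baseline measurements as covariates, will be performed for all studied variables", which would take in those two counts.

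**The concern.** A comparison of harms between randomised arms is fair only if an event has the same chance of being recorded in each arm. A rule that admits an event only when it is related to the intervention puts a causal judgement ahead of the record. An event judged unrelated leaves no trace, so the judgement cannot be reviewed later. If the intervention means exoskeleton training, a control participant with the same skin injury has no clear route into the record.

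The participants have an EDSS score of 4.5 to 7 and need canes or crutches outdoors. The Discussion expects the trial to show what patients can tolerate and to support guidelines. Without a background rate recorded in the same way, a count of skin injuries in the OR arm would be hard to interpret.

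**Working it through.** The document gives no adverse-event figure to reproduce, so the check is of the text, with a little arithmetic at the end.

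**Step 1: what the relatedness phrase attaches to.** In "All co-existing diseases or conditions related to the intervention will be treated according to prevailing medical practice" it may qualify both nouns or only the second.

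**Step 2: what the intervention is.** The randomisation section assigns people to "either the control group (CG) or the intervention group (OR", and Sample Size Calculation sets intervention against control. The abstract, the aims, the OR section and the Discussion also use the word for the exoskeleton arm. Against this, the control arm's section is headed "Control Group Intervention (CG", and Statistical Considerations speaks of training interventions in the plural. The OR-only sense is the commoner one, but not the only one.

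**Step 3: combine the two.**

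| Phrase qualifies | Intervention means | Consequence |
|---|---|---|
| Both nouns | OR training only | OR events need a causal judgement; control events have no route in |
| Both nouns | Either arm's treatment | Both arms can contribute, but only after a causal judgement |
| Conditions only | OR training only | Co-existing disease counts in both arms, including disease present at entry; a control-arm skin injury does not |
| Conditions only | Either arm's treatment | Co-existing disease counts in both arms; other conditions still need a causal judgement |

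In none of the four rows is a new condition such as a skin injury reported in both arms irrespective of cause. Even in the second and fourth rows capture may differ. Both arms receive the same physiotherapy, but the OR arm adds two supervised sessions a week for 3 months. Taking 3 months as 12 to 13 weeks, that is 2 × 12 = 24 to 2 × 13 = 26 further occasions on which an event can be seen and attributed.

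**Step 4: what is captured elsewhere.** Falls and outbreaks are counted without a relatedness filter. Fatigue is scored on the MFIS, and pain or discomfort is a EuroQol-5 domain, in both arms, though as scales rather than events. Skin injury, which Safety Assessments names itself, has no separate measure.

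**Step 5: what numbers can and cannot show.**
- With 18 participants in an arm and no events, the exact upper 95% bound on the risk is 1 − 0.05^(1/18) = 15.3% (one-sided), or 1 − 0.025^(1/18) = 18.5% (two-sided). This follows from the arm size under any definition, so it does not measure the defect.
- For 18 against 18, at two-sided 5% and with a pooled normal approximation, power = Φ[(|p₁ − p₂| − 1.96·√(2p̄(1 − p̄)/18)) / √((p₁(1 − p₁) + p₂(1 − p₂))/18)]. The event rates are assumed for illustration. For 10% against 30%: (0.200 − 1.96 × 0.1333)/0.1291 = −0.475, power 32%. For 10% against 50%: (0.400 − 1.96 × 0.1528)/0.1374 = 0.73, power 77%.

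So even perfect recording would support a description with intervals, not a firm test.

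**The case against.** The best case for the plan has five parts.

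1. A reader might infer that control-arm events cannot count, or that the control rate is zero by definition. The text does not say so. That needs two readings at once, as in the first row of the table, while the section speaks of a participant without naming an arm. Even then the control rate would be uncollected, not zero. This part of the objection stands.

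2. A reader might infer that the trial cannot compare safety between arms. That is also too strong: falls, one of the two examples in Safety Assessments, and outbreaks can be compared, and fatigue and pain are scored in both arms. This stands too.

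3. A reader might say that unblinded treating staff judge relatedness. The article does not say who judges it. Outcome assessors are blinded, and the physiotherapists running exoskeleton sessions necessarily know the allocation, but that their judgement decides is an assumption.

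4. A between-arm safety comparison is not among the stated aims. That is correct and limits the weight of the point.

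5. An article condenses the full protocol, so definitions and causality grading may sit there. That would answer a complaint about missing detail. It does not answer a rule that is printed and that, on each reading, makes some new conditions depend on attribution.

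**Conclusion.** The point holds in a limited form. The adverse-event rule is ambiguous, and on every reading at least some new conditions are reported only if judged related to the intervention, a term mostly used for the OR arm. Events other than falls and outbreaks, with skin injury the clearest example, may therefore be captured unequally. If the phrase attaches only to conditions, co-existing disease present at entry would also be reported as an adverse event.

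The direction and size of any resulting bias cannot be derived from the document: they depend on who judges relatedness and how, which is not stated. The gait-speed analysis is untouched. The wording should be corrected because the change is cheap and the remaining harms data otherwise rest on an unrecorded judgement, but it does not call the design into question. The conclusion assumes that the printed rule is the one in use.

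**What to change.** Replace the reporting sentence with wording to this effect: *Any new or worsened medical event from randomisation to T3 is recorded in both arms, regardless of presumed cause, using the same questions at T2 and T3. Relatedness, severity and seriousness are recorded as attributes of each event. Conditions present before randomisation are medical history.* The statement on how conditions are treated need not change.

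Report by arm the number of events and the number of participants with at least one event, with exact confidence intervals. List events noted only during exoskeleton sessions separately, outside the between-arm comparison. Asking at every session attended would give the OR arm more enquiries and bring back the imbalance.

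The cost is slightly more recording at two visits that already take place. Trial Status says that the trial is under way, so participants already treated would have to be asked in retrospect. Their capture will be incomplete, and the report should say so.

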### Sample Size Calculation

Sample size has been calculated to detect a clinically meaningful change in gait speed: accepting an alpha risk of 0.05 and a beta risk of 0.20 in a bilateral contrast, 32 subjects are required to detect a difference equal to or greater than 0.1 m/sec speed in the 10 meters timed walking test (SD = 0.16). Sample size has been increased an additional 12% to account for losses during follow-up. The resulting sample size is 36 subjects, therefore 18 individuals per group (intervention and control group).

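### The 32 evaluable subjects do not follow from the stated sample-size inputs: an unadjusted two-sided, two-arm comparison needs 82 to 84, and 32 give about 40% power if 0.16 is the SD of the analysed quantity

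*Protocol article*

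**What the plan says.** The Sample Size Calculation section gives a full set of inputs. The error rates are set by "accepting an alpha risk of 0.05 and a beta risk of 0.20 in a bilateral contrast". The target difference is described as clinically meaningful, the SD is 0.16, and the conclusion is that "32 subjects are required to detect a difference equal to or greater than 0.1 m/sec speed in the 10 meters timed walking test". The losses step follows: "Sample size has been increased an additional 12% to account for losses during follow-up". The section closes with "The resulting sample size is 36 subjects, therefore 18 individuals per group (intervention and control group". The 36 is therefore the total over both groups, and so is the 32 it is built from: 16 evaluable per arm.

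Other sections fix the comparison. Study Design and Participants describes a randomised parallel-group trial with assessments at T1 (baseline), T2 (3 months) and T3 (6 months), and the recruitment section sets 1:1 allocation. The Introduction gives the aim as the effect on gait speed of adding the exoskeleton programme to conventional rehabilitation, which is a between-group question. Statistical Considerations plans mixed-design ANCOVA with the baseline value as covariate (or a Friedman test). The sample-size paragraph does not refer to that adjustment, gives no correlation, and does not say whether 0.16 is the SD of raw speed, of change, or a residual SD.

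**The concern.** The target is 0.1/0.16 = 0.625 SD. Sixteen per arm is the usual answer for a difference of about one full SD, so the total looks too small by a factor of about 2.5 (82/32 = 2.6).

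This is the power claim for the primary outcome. The limitations paragraph of the Discussion warns that the sample may be too small only for the secondary outcomes, so a reader has no reason to doubt the primary one. If power for 0.1 m/s is well below 80%, a non-significant gait-speed result says much less about that effect than the stated beta risk implies.

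**Working it through.** **Inputs** (all from Sample Size Calculation unless noted): two-sided alpha 0.05 (z = 1.960); power 0.80 (z = 0.842); difference 0.1 m/s; SD 0.16 m/s; 32 evaluable in total, 36 enrolled; 1:1 allocation (recruitment section).

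**1. Trying to reproduce 32 as a two-sided, two-arm calculation**

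n per arm = 2 × (1.960 + 0.842)² × (0.16/0.1)² = 2 × 7.849 × 2.56 = 40.2, so 41 per arm and 82 in total. With the t-test the solution is 41.2, so 42 per arm and 84 in total (power 79.8% at 41, 80.8% at 42). The stated 32 is not reproduced.

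**2. Other readings**

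| Reading | Result | Fits the text? |
|---|---|---|
| 32 per arm, two-sided | power 69% (t), 71% (normal) | No: below 80%, and the text gives 18 per group |
| One-sample or paired, two-sided | 21 (z), 23 (t) | No: not 32, and not between groups |
| Two-sample, one-sided | 31.7, so 32 per arm (64 in total) | No: contradicts the two-sided statement and 18 per group |
| One-sample, one-sided | 15.8, so 16 per group (32 over two) | No: neither two-sided nor between groups |

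The two one-sided rows match 32 numerically and may show where it came from. That is an inference.

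**3. What 32 delivers if 0.16 is the SD of the analysed quantity** (follow-up value, change or residual; noncentral t)

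- Standard error of the difference at 16 per arm: 0.16 × √(2/16) = 0.0566; noncentrality 0.1/0.0566 = 1.77; power 40.2% (normal approximation 42.4%).
- At 18 per arm, with no losses: power 44.5% (normal approximation 46.6%).
- Difference detectable with 80% power: 0.164 m/s at 16 per arm, 0.154 m/s at 18 per arm.
- Expected 95% CI half-width at 16 per arm: 2.042 × 0.0566 = 0.116 m/s, wider than the 0.1 m/s target.

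**4. What 32 delivers if 0.16 is the SD of raw gait speed**

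Baseline adjustment at one follow-up visit leaves a residual SD of 0.16 × √(1 − r²), where r is the baseline to follow-up correlation. The article gives no r, so these values are assumptions (16 per arm, 29 df):

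| r | Residual SD | Power for 0.1 m/s |
|---|---|---|
| 0.5 | 0.139 | 51% |
| 0.6 | 0.128 | 57% |
| 0.7 | 0.114 | 67% |
| 0.8 | 0.096 | 81% |

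On this reading 80% needs r of about 0.79. If the group effect is averaged over T2 and T3, and one further assumes equal correlations among the three visits and a constant effect, the variance factor is (1 + r)/2 − r². Power is then 68% at r = 0.5, 73% at 0.6 and 81% at 0.7, and r of about 0.69 is enough for 80%.

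**5. Attrition step**

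32 × 1.12 = 35.84, so 36, as printed.

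**The case against.** The strongest counter-argument is that the planned analysis is not an unadjusted comparison. Statistical Considerations specifies ANCOVA with baseline as covariate and there are two post-baseline visits. If 0.16 describes raw gait speed and repeat measurements correlate strongly, 32 evaluable subjects could have close to 80% power. The article also condenses a fuller protocol, where a correlation may be given.

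This stands in part. It means that 40% is a conditional figure, and that r = 0.79 is not a floor for a model that uses both follow-up visits. The missing correlation is not held against the article as a separate omission. It does not rescue the paragraph, which prints inputs and a result and presents one as following from the other. No adjustment enters that calculation.

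Four stronger readings are tempting, and the documents do not support them:

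- **That the trial will miss a 0.1 m/s effect more often than not.** This is true only if 0.16 is the SD of the analysed quantity. With raw SD 0.16 and adjustment, power already passes 50% at r = 0.5.
- **That no conventional formula gives 32.** One-sided formulas do. They conflict with the text, so the accurate statement is limited to two-sided, two-arm readings.
- **That the attrition step is also wrong because 32/0.88 = 36.4, so 37.** The text describes a 12% increase, and 36 is right on that convention.
- **That a null result will be reported as absence of effect.** The article states no such interpretation rule.

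**Conclusion.** The point holds as an arithmetic inconsistency in the primary power statement. The printed inputs require 82 to 84 evaluable subjects for an unadjusted two-sided comparison of two equal arms, against 32 stated. This part needs no assumption beyond the inputs in the article.

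The power actually available depends on what 0.16 measures. It is about 40% (16 per arm) to 44.5% (18 per arm) if 0.16 is the SD of the analysed quantity. It is higher if 0.16 is the SD of raw speed: about 51% to 81% for assumed correlations of 0.5 to 0.8 at one visit, and more if the effect is averaged over T2 and T3. The article does not allow a choice between these cases, so 80% power is unsupported as written but not shown to be unattainable.

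**What to change.** Keep 36 participants and rewrite the Sample Size Calculation paragraph in one of two ways, according to what 0.16 represents:

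- **SD of the analysed quantity:** state that 32 evaluable participants (16 per arm), with SD 0.16 and two-sided alpha 0.05, give about 40% power for 0.1 m/s and 80% power for about 0.16 m/s.
- **Baseline adjustment intended:** state that 0.16 is the SD of raw gait speed, give the assumed correlation and its basis, name the visit or visits the contrast uses, and report the resulting power.

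In either case, add that a non-significant primary result will be interpreted from its 95% confidence interval against 0.1 m/s. Leave the 12% attrition step unchanged.

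The cost is one reworded paragraph and, unless a high correlation can be justified, a less favourable power statement. The trial was already under way according to Trial Status, and this change adds no participants and no assessments.
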